#### 2.6 Randomization and Consent

Research personnel (research coordinators and/or RTs) will identify, consent (where applicable) and enroll eligible patients from Monday to Friday during regular hours using a central randomization system, stratified by ICU with variable undisclosed block sizes. Patients will be randomized to a screening frequency (once vs. at least twice daily) AND an SBT technique (PS + PEEP vs. T-piece). The day of randomization will be considered study day one.

Given the minimal risk associated with the interventions being evaluated (screening frequency and SBT conduct) and the need to enroll patients as soon as possible after they initiate spontaneous breaths or trigger breaths, we will request ethics approval to use a hybrid consent model that prioritizes patient (with decision-making capacity) or SDM consent (when available) and permits deferred consent in their absence.

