## 2.10 Outcomes

**2.10.1 Primary Outcome:** Aligned with our survey results [24] and informed by discussions with our PFAC, the primary outcome will be the *time to successful extubation* – signalling timely and safe liberation from the ventilator. Successful extubation is defined as the time when unsupported, spontaneous breathing BEGAN and was sustained for  $\geq 48$  hours after extubation/disconnection in patients with tracheostomy [38].

**2.10.2 Secondary Outcomes:** We prioritize secondary outcomes that are patient-centred [42] and important to citizens including: [1] Time to first passing an SBT, [2] ICU mortality, [3] Hospital and 90 day mortality [31], [4] Total duration of mechanical ventilation (invasive and noninvasive), [5] ICU length of stay, [6] Hospital length of stay, [7] Use of NIV after extubation, [8] VAP, [9] adverse events, self-extubation, tracheostomy, reintubation, prolonged ventilation at d14 and d21, ICU readmission [32,33], [10] proportion receiving sedation/ analgesia/ antipsychotics at key time points or [11] screened positive for delirium at key time points, [12] HRQoL (EuroQoL EQ-5D) 6 months after randomization [34], [13] functional status 6 months after randomization using the FIM [35-37].

**2.11 Analytic Plan:** We will summarize baseline data using descriptive statistics [43]. All analyses will be performed adhering to the intention-to-treat principle.

**2.11.1 Primary Analysis:** Time-to event outcomes present special challenges because death is a competing risk and survivor only analyses are improper sub-groups. We will construct cumulative incidence curves to provide outcome estimates accounting for death for screening frequency and SBT technique. Cause-specific treatment effects will be depicted with hazard ratios (HR) (95% CI) from Cox models.

**2.11.2 Secondary Analysis:** We will report treatment effects in time to event analyses using HR and odds ratio (OR) with 95% CIs for binary outcomes and mean difference for continuous outcomes [43].

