**2.11.3 Exploratory and Adjusted Analyses:** To assess the effect of age (continuous variable) by treatment interaction on the HR of time to successful extubation, we will construct a Cox regression model using a restricted cubic spline for age. Instead of arbitrarily assigning different levels for each age group, period, and cohort, a smoothing function or spline [collections of cubic polynomials joined smoothly at predefined number of points (knots)] will be created. The number of knots is expected to be between 3 and 5 but will be selected based on the sample size assuming the relationship with age will change gradually and smoothly. We will evaluate fitting using bootstrap techniques. As an extension of linear models, this technique allows for nonlinearities and interactions (between variables) that are more flexible than the linear contrasts traditionally used in regression models and is easier to depict and interpret [44]. In exploratory analyses, we will assess for an interaction between screening frequency and SBT technique. In adjusted analyses, we will consider variables (e.g., COPD, frailty score etc.) of potential prognostic importance.

**2.11.4 Interim Analyses:** Interim analyses for safety (adverse events) and efficacy (primary outcome) will be performed at 25%, 50% and 75% of accrual. Given the risks of stopping early for benefit, statistical significance will be declared using small p-values according to the O'Brien-Fleming boundaries for the primary outcome (time to successful extubation) and reintubation rate [45].

**2.11.5** In lieu of the emerging COVID-19 pandemic, we will enroll up to 250 additional critically ill patients who test positive for COVID-19 alongside the originally planned 760 (COVID-19 negative) patients. In this manner, we will be able to report on weaning and clinical outcomes in COVID-19 positive and COVID-19 negative patients combined and separately. The primary, secondary, exploratory, and adjusted analyses will report on 760 COVID-19 negative patients. We will also report the primary and secondary outcomes in COVID-19 positive patients alone and with both cohorts (COVID-19 positive and negative) combined.

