**2.12.2 Sample Size Estimate:** To take into consideration deaths before successful extubation, we used cumulative incidence curves generated from our pilot trials and computed 3 mortality HRs per patient day [HR 2.9% (Release Trial) and HR 3.3% (SENIOR Trial) and HR 3.2% (combined)] to compute the sample size [27]. To demonstrate a reduction in time to successful extubation from a median of 5.0 days to 4.0 days [HR 1.25] [38,46] with 80% power and  $\alpha = 0.05$ , and allowing for 3 interim analyses, the proposed trial would require 760 patients. *A priori*, we do not expect an interaction since mechanistically and sequentially an interaction is very unlikely. Since the groups are orthogonal, the main effects (in the absence of interactions) will have the same power to detect the same size differences (see Sample Size Table below).

| Median time
(Once daily) | Median time (At Least
Twice daily) | Hazard
Ratio | Power      | Alpha       | N           |
|-----------------------------|---------------------------------------|-----------------|------------|-------------|-------------|
| 5.0 days                    | 4.2 days                              | HR 1.19         | 80%        | 0.05        | 1244        |
| 5.0 days                    | 4.1 days                              | HR 1.22         | 80%        | 0.05        | 960         |
| 5.0 days             | 4.0 days                       | HR 1.25  | 80% | 0.05 | *760 |
| 4.5 days                    | 3.4 days                              | HR 1.32         | 80%        | 0.05        | 472         |
| 4.0 days                    | 3.5 days                              | HR 1.14         | 80%        | 0.05        | 2064        |

**2.13 Timeline:** The trial will be conducted in 7 phases over 54 months: (i) start-up/recruitment (31 months), (ii) 6 month follow-up assessments (months 11 to 37), (iii) data cleaning (months 32-40), (iv) trial close out

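### Randomisation is stratified by ICU, but the primary Cox models are not stated to account for ICU; if ICUs differ, an unadjusted model loses power and moves the HR toward 1

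*Combined protocol and SAP*

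**What the plan says.** Section 2.6 describes allocation "using a central randomization system, stratified by ICU with variable undisclosed block sizes". Section 2.11.1 plans cumulative incidence curves that account for death, and then gives the whole model specification in one sentence: "Cause-specific treatment effects will be depicted with hazard ratios (HR) (95% CI) from Cox models". It names no stratum, covariate, frailty term or clustered variance, and does not say whether screening frequency and SBT technique enter the same model.

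Section 2.11.3 places adjustment outside the primary analysis: "In adjusted analyses, we will consider variables (e.g., COPD, frailty score etc.) of potential prognostic importance". The list is open, and ICU is not on it. Section 2.11.4 tests the primary outcome at 25%, 50% and 75% of accrual with O'Brien-Fleming boundaries, again without defining the model.

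Section 2.12.2 sets the effect from overall medians of 5.0 and 4.0 days (HR 1.25) and a combined death rate of 3.2% per patient-day, with 80% power and alpha 0.05. It concludes, "allowing for 3 interim analyses, the proposed trial would require 760 patients". No ICU term enters that calculation, and no between-ICU variance is given anywhere.

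**The concern.** Blocking within ICU balances the arms within each ICU. If ICUs differ in how fast patients are extubated, that balance makes the treatment estimate vary less from trial to trial than an unadjusted model assumes. The unadjusted standard error is then too large for the design, and the test rejects too rarely. Separately, the hazard ratio is non-collapsible: leaving out a prognostic factor moves the estimate toward 1 relative to the within-ICU HR, even with perfect balance.

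The protocol gives reasons to expect ICU differences. Section 1.4 cites practice variation, and 1.3.2 reports that physicians keep authority over extubation. Section 3.1.6 lists 10 Canadian and 10 US ICUs, 17 academic and 3 community. Section 2.7 leaves extra screens in the more frequent arm to clinicians, and 2.7.2 allows SBTs of 30 to 120 minutes.

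At stake are some of the planned power and the meaning of the reported HR. Prespecification is also at stake: in an unblinded trial with three interim looks, the handling of ICU should not be left open until data are in hand.

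**Working it through.** **Inputs.** From 2.12.2: medians 5.0 and 4.0 days, death hazard d = 0.032 per day, power 80%, alpha 0.05 (taken as two-sided). From 2.9: follow-up to day 60. From 1.5: 760 patients in 20 ICUs, or 38 per ICU on average. Assumed, because the documents do not give it: the SD of ICU log-hazards of extubation, from 0 to 0.7.

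**Reproducing the plan's N.**
- Extubation hazards are ln 2/5 = 0.1386 and ln 2/4 = 0.1733, a ratio of 1.25.
- Events needed (Schoenfeld): 4(1.960 + 0.842)²/(ln 1.25)² = 631. One-sided alpha would need only 497, which does not fit the plan's N.
- Probability of extubation before death by day 60: l/(l+d) × (1 − exp(−60(l+d))) = 0.812 and 0.844, mean 0.828.
- N = 631/0.828 = 762. An assumed O'Brien-Fleming inflation of about 1.024 gives 781. Both are within 3% of 760.
- At 760 patients, 629 events are expected: √629/2 × 0.2231 − 1.960 = 0.838, a power of 79.9%.

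The planning figures therefore hold for a model with no ICU variation.

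**What the assumed SDs mean.** Around a 5-day median, ICUs one SD either side of average have medians of 5 × exp(±SD): about 3.7 to 6.7 days at SD 0.3, and 3.4 to 7.5 days at SD 0.4.

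**Adding ICU variation.** The simulations used 760 patients in 20 ICUs, permuted blocks within ICU, exponential extubation with a within-ICU HR of 1.25, death at 0.032 per day, normal ICU effects on the log hazard and no interim looks. Ranges cover separate sets of 2,000 to 4,000 runs per setting, with Monte Carlo error of about 0.7 to 1 point on power.

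| ICU SD | Mean unadjusted HR | Power, unadjusted | Power, Cox stratified by ICU | Power, ICU frailty |
|---|---|---|---|---|
| 0 | 1.25 | 80-81% | 76-78% | 80% |
| 0.2 | 1.24 | 77-78% | 75-77% | 79% |
| 0.3 | 1.23-1.24 | 74-75% | 76-77% | 78% |
| 0.4 | 1.22-1.23 | 70-72% | 74-76% | 78% |
| 0.5 | 1.21-1.22 | 67-69% | 75-76% | 78% |
| 0.7 | 1.19 | 59-60% | 76% | 78% |

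The stratified and frailty HRs stay at about 1.25. The frailty variance was treated as known, so that column is slightly optimistic.

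**Why strata are not free.** Splitting into 20 strata raises the standard error of the log HR from 0.080 to 0.084. With no ICU variation, 0.2231/0.084 − 1.960 = 0.696, a power of about 76%. Stratification breaks even near SD 0.2 to 0.3.

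**Under the null.** At a nominal 5%, the unadjusted test rejected 3.8-4.1% of the time at SD 0.3 and 3.5% at SD 0.5. The frailty model rejected 4.7% and 5.3%. ICU fixed effects gave 79-80% power, but a slightly high HR (about 1.26) and 5.3-5.7% rejection under the null.

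**If 1.25 is the overall HR.** At SD 0.4, a within-ICU HR of 1.28 gives an unadjusted HR of 1.25 and 81% unadjusted power.

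**The case against.** The strongest reply has four parts.

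1. A reader might infer that the sponsor chose to leave ICU out. The documents do not say so. Section 2.11.1 is silent and 2.11.3 leaves its list open. Part of the document between the recruitment table in 2.13 and section 3.1.5 was not available and is not judged. This stands: the point is that the handling of ICU is not stated. The visible text, followed literally, still yields an unadjusted model.

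2. The harm depends on a variance the documents do not supply. The plan also standardises much of care: screening criteria (2.7.1), SBT failure criteria (2.7.2), extubation criteria (2.7.4), and guidance on titration, NIV, reintubation and tracheostomy (2.7.5). This stands as a limit on size. At SD 0.2 or below the loss is at most about 3 points. Standardisation may reduce ICU differences but does not show that they are absent.

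3. A reader might infer that the trial falls short of 80% power and that its HR is biased. That holds only if 1.25 is a within-ICU HR. It was set from overall medians, and the marginal and within-ICU HRs are different quantities. On the marginal reading there is no material shortfall. The documents do not settle which is meant, and the conservative test remains on either reading.

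4. A reader might think that leaving ICU out saves nothing. Against a Cox model stratified by 20 ICUs that is wrong: with no ICU variation, the unadjusted model keeps 2 to 4 points more power. It is close to right only against a frailty term.

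**Conclusion.** The point holds as a conditional one. The trial randomises within ICU, and the primary model is not stated to use that factor. If ICUs differ and 1.25 is the within-ICU effect, an unadjusted model gives up about 3 points of power at SD 0.2, 5 at SD 0.3 and 11 to 13 at SD 0.5, and reports an HR of roughly 1.24, 1.23 and 1.21-1.22. With no ICU variation there is no loss. These figures rest on assumed ICU SDs, exponential times and no interim looks.

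Validity is not threatened: the unadjusted test errs on the conservative side, and nothing here suggests inflated type I error. Whether both randomised factors share one model is also unstated. No size is attached to that, and 2.12.2 treats the factors as orthogonal. The change is worth making because a frailty term costs almost nothing and protects power, and because the target HR should be named in advance.

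**What to change.** In 2.11.1, state the primary model as a cause-specific Cox model containing both screening frequency and SBT technique, with a prespecified shared-frailty term for ICU. State that the reported HR is the within-ICU effect. Use the same model at the interim and final analyses and for the time-to-event secondary outcomes, and report the unadjusted HR as a sensitivity analysis.

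The cost is a few lines of text, since ICU is already recorded for randomisation. The loss of power from a frailty term is close to nil if ICUs hardly differ. Stratifying the Cox model by the 20 ICUs is a workable alternative, but it would cost about 2 to 4 points of power in that case.

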#### 2.5 Exclusion Criteria

- (1) Brain death or expected brain death.
- (2) Evidence of myocardial ischemia in the 24 hour period before enrollment.
- (3) Received continuous invasive mechanical ventilation for  $\geq 2$  weeks.
- (4) Tracheostomy in situ at the time of screening.
- (5) Receiving a sedative infusion(s) for seizures or alcohol withdrawal.
- (6) Require escalating doses of sedative agents.
- (7) Receiving neuromuscular blockers or who have known quadriplegia, paraplegia or 4 limb weakness or paralysis preventing active mobilization.
- (8) Moribund (e.g., at imminent risk for death) or who have limitations of treatment.
- (9) Profound neurologic deficits (e.g., post cardiac or respiratory arrest, large intracranial stroke or bleed) or Glasgow Coma Scale (GCS)  $\leq 6$ .
- (10) Use of ventilator modes that automate SBT conduct.
- (11) Currently enrolled in a confounding study that includes a weaning protocol.
- (12) Previous enrollment in this trial.
- (13) Previous SBT or are already on T-piece, or CPAP alone (without PS), or PS  $\leq 8$  cm  $\text{H}_2\text{O}$  regardless of PEEP, or other 'SBT equivalent' settings immediately before randomization.
- (14) Previous extubation [planned, unplanned (e.g. self, accidental)] during the same ICU admission.

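### The primary Cox models name no baseline covariate; fixing a short list before the first interim look is a cheap gain in power, of a size the documents do not determine

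*Combined protocol and SAP*

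**What the plan says.** **Primary analysis (section 2.11.1).** Cumulative incidence curves are drawn with death as a competing event, and "Cause-specific treatment effects will be depicted with hazard ratios (HR) (95% CI) from Cox models". No covariate is named. The text does not call the models unadjusted; it is silent.

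**Exploratory and adjusted analyses (section 2.11.3).** For the age-by-treatment interaction, "we will construct a Cox regression model using a restricted cubic spline for age". For everything else: "In adjusted analyses, we will consider variables (e.g., COPD, frailty score etc.) of potential prognostic importance". COPD and frailty are examples, not a fixed list.

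**Entry criteria (sections 2.4 and 2.5).** Patients need at least 24 hours of ventilation and are excluded if they "Received continuous invasive mechanical ventilation for $\geq 2$ weeks". Days ventilated before randomisation must therefore be known for every patient.

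**Sample size (section 2.12.2).** The target is a fall in median time to successful extubation from 5.0 to 4.0 days, HR 1.25, "with 80% power and" alpha 0.05; "allowing for 3 interim analyses, the proposed trial would require 760 patients". Covariate adjustment is not mentioned.

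**The concern.** If a Cox model leaves out a baseline variable that predicts the outcome, its treatment hazard ratio lies closer to 1 than the hazard ratio given that variable. This happens even under perfect randomisation. The standard error hardly falls to compensate, so the unadjusted test has less power than the adjusted one.

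The trial is sized at 80% with no visible margin, and power is expensive here: in the plan's own sample size table, moving from HR 1.25 to HR 1.22 raises the requirement from 760 to 960. Variables that are known at entry, or that the plan itself names as possibly prognostic, might buy back some power without any extra patients.

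**Working it through.** **Inputs from the documents.** Medians 5.0 and 4.0 days, HR 1.25, 80% power, alpha 0.05, N = 760, death rate 3.2% per patient-day (combined pilots; section 2.12.2); follow-up to day 60 (section 2.9); three interim looks with O'Brien-Fleming boundaries (section 2.11.4).

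**Assumptions.** Two-sided test (sidedness is not stated; one-sided 0.05 would give N = 601, which does not match 760). Equal allocation within each factor. Exponential times.

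**1. Reproduce 760.**
- Events by Schoenfeld's formula: D = 4(1.96 + 0.8416)² / (ln 1.25)² = 4 × 7.849 / 0.04979 = 631.
- Probability of extubation before death: control 0.1386 / (0.1386 + 0.032) = 0.8125; intervention 0.1733 / (0.1733 + 0.032) = 0.8441; mean 0.8283.
- N = 631 / 0.8283 = 762, against 760 stated. A factor of 1.02 for the interim looks gives 778, within 3%.

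**2. Power at 760.** Expected events are 760 × 0.8283 = 629.5. Power is Φ(√(629.5/4) × ln 1.25 − 1.96) = Φ(0.839) = 79.9% for a fixed design, and about 79% with four O'Brien-Fleming analyses.

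**3. Effect of leaving out prognostic covariates.** One standard normal baseline score stands for all prognostic variables together. A patient's extubation hazard is λ₀ · exp(β · arm + SD · score), with λ₀ set so that the control median stays at 5.0 days. Other settings: death 0.032 per day, deaths censored, cut-off at day 60, 760 patients, fixed-sample two-sided 0.05 test, 2,500 simulated trials per setting (Monte Carlo standard error just under 1 point). The documents give no value for SD, so a range is shown. SDs of 0.20, 0.35 and 0.50 correspond to hazard ratios of 1.22, 1.42 and 1.65 per SD of the score.

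*Reading A: 1.25 is the hazard ratio given the covariates.*

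| SD | Unadjusted HR | Events | Power unadjusted | Power adjusted |
|---|---|---|---|---|
| 0 | 1.248 | 630 | 79.5% | 79.4% |
| 0.20 | 1.241 | 628 | 77.0% | 79.6% |
| 0.35 | 1.228 | 624 | 72.4% | 79.0% |
| 0.50 | 1.212 | 617 | 65.9% | 79.0% |

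Hand check with the formula of step 2. SD 0.20: Φ(√(628/4) × ln 1.241 − 1.96) = Φ(0.745) = 77%. SD 0.35: Φ(0.604) = 73%. SD 0.50: Φ(0.429) = 67%. All lie within about 1 point of the simulation.

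*Reading B: 1.25 is the marginal (unadjusted) hazard ratio.* The conditional HR is raised until the unadjusted one is about 1.25. At SD 0.50, for example, the attenuation factor under reading A is ln 1.212 / ln 1.249 = 0.865, so the conditional HR is exp(0.2231 / 0.865) = 1.294.

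| SD | Conditional HR | Power unadjusted | Power adjusted |
|---|---|---|---|
| 0.20 | 1.258 | 77.6% | 80.3% |
| 0.35 | 1.273 | 77.8% | 83.7% |
| 0.50 | 1.294 | 76.5% | 88.5% |

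Unadjusted power is a little under 80% here because events fall slightly, the realised unadjusted HR is 1.246 to 1.248, and there is simulation error.

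**4. Comparison.** The gain from adjustment is about 3, 7 and 13 points under reading A and about 3, 6 and 12 points under reading B. It is nil at SD 0. Adjustment does not lose power under either reading.

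**The case against.** The case for leaving the plan alone is substantial.

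- **The effect size is stated without adjustment.** HR 1.25 is given beside arm-level medians from earlier trials, and 760 follows from putting it straight into the events formula. If it is the marginal HR, unadjusted power stays near plan and adjustment is a bonus, not a repair. This stands: the falls to 72% and 66% belong to reading A only, and no section says that 1.25 is conditional.
- **Prognostic strength is unknown.** The pilot table in section 1.3.3 shows no consistent age effect. The elderly pilot had the longer median under once-daily screening (6.83 against 5.0 days) but the shorter one under more frequent screening (3.10 against 3.76). These arms are small, but they do not support a large SD. This stands.
- **The simulation is a best case.** It uses one perfectly measured score in the correct functional form. A real model would have a spline, an indicator and a frailty score with some values missing. Interim looks were not simulated. This stands.
- **An unadjusted primary analysis is legitimate.** A reader might infer that the primary hazard ratio is biased toward 1. It is not: the shift is non-collapsibility, meaning that the marginal and conditional hazard ratios are different quantities. The type I error rate is not affected either.
- **The covariates are not shown to be in use.** Age enters only as an effect modifier, and COPD and frailty are only candidates. The documents do not confirm that a frailty score is collected at baseline.
- **Late choice of covariates.** A reader might infer that the open list lets the primary result be picked after the data are seen. It affects only the non-primary adjusted analysis, since a primary model without covariates leaves nothing to choose. Section 2.13 also schedules a published protocol and analytic plan for month 6, where a list could be fixed.

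These points limit the size and the wording. None shows that pre-specified adjustment would harm validity or power.

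**Conclusion.** This is a cheap improvement, not a defect. The primary Cox models are stated without baseline covariates, and a pre-specified adjusted model would have at least as much power under either reading of HR 1.25. The gain is about 3 points if the covariates are weak (SD 0.20) and about 12 to 13 points if they are strong (SD 0.50). It depends wholly on a prognostic strength that the documents do not give, and the figures are upper-end values for a correctly modelled, fully measured score.

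A reader might infer that the trial is underpowered or that 760 is wrong. The documents do not support that: 760 reproduces to within two patients from the plan's inputs, and unadjusted power falls well below 80% only if 1.25 is taken as conditional and the covariates are at least moderately prognostic.

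The text between sections 2.13 and 3.1.5 was not available and could not be checked for further detail on covariates.

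**What to change.** Before the first interim efficacy look (25% of accrual), state in section 2.11.1 that:

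- the primary cause-specific Cox model for each factor includes both randomised factors and a short fixed list of baseline covariates: age (the restricted cubic spline already planned can be reused), days ventilated before randomisation, and COPD and frailty score if these are collected at baseline;
- missing baseline values are handled by a simple stated rule, such as single imputation from baseline data;
- the same model is used at every interim look and in the final analysis;
- the unadjusted HR is reported as supporting, and the cumulative incidence curves stay unadjusted.

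In section 2.12.2, say whether HR 1.25 is marginal or conditional.

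The cost is plan wording only, with no extra patients and no new data for age or days ventilated. There are two small drawbacks: the primary HR becomes conditional on the covariates, and missing frailty scores need handling. Timing matters because the trial is unblinded and tests efficacy repeatedly; changing the model after a look would change the test statistic partway through the sequence.

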More than two decades of research support the use of specific strategies to limit patient's exposure to invasive ventilation including the (i) use of multidisciplinary screening protocols [to identify candidates for a spontaneous breathing trial (SBT)] [9-11], (ii) conduct of SBTs [12-14] to test patient's ability to breathe with limited or no support, and (iii) use of specific modes [reductions in Pressure Support (PS)] or techniques [once daily SBTs with PS  $\pm$  positive end expiratory pressure (PEEP) or T-piece (no inspiratory or expiratory support)] [15-17] to decrease support in patients who fail an initial SBT. Compared to *usual care*, randomized trials and our meta-analysis suggest that protocolized weaning, led by allied health care providers [Respiratory Therapists (RTs) and nurses], reduced weaning time and ICU stay [12-14,18]. *Although a credible body of weaning evidence exists, it is insufficient to guide current practice.*

**1.1 The Weaning Paradox:** To improve outcomes and reduce complication rates, clinicians strive to shorten patients' exposure to invasive ventilation. However, premature or failed attempts at extubation necessitating reintubation are associated with morbidity (VAP) and an 8 to 10 fold increase in mortality [19]. *In their efforts to minimize patients' exposure to invasive ventilation, clinicians are challenged by a 'trade-off' between the risks associated with a premature failed attempt at extubation (too early) and the complications associated with protracted invasive ventilation (too late).*

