## 2.0 Research Approach and Methods

**2.1a) Primary Objectives:** The primary objectives of the FAST trial are to demonstrate the effect of:

- (i). The alternative screening strategies ('once' vs. 'at least twice' daily) on time to successful extubation.
- (ii). The alternative SBT techniques (T-piece vs. PS + PEEP) on time to successful extubation.

**2.1b) Secondary Objectives:** In secondary objectives, we will obtain estimates of the impact of the alternative screening and SBT techniques on clinically important outcomes including time to first passing an SBT, ICU mortality, hospital and 90 day mortality [31], total duration of mechanical ventilation, ICU and hospital length of stay, use of noninvasive ventilation (NIV) after extubation, VAP, adverse events, self-extubation, tracheostomy, reintubation, prolonged ventilation at day14 and 21, ICU readmission [32,33], proportion receiving sedation/ analgesia/ antipsychotics or screened positive for delirium at key time points, health related quality of life (HRQoL)(EuroQuol EQ-5D) and a functional status assessment [the Functional Independence Measure (FIM)] assessed 6 months after randomization [34-37].

**2.2 'A Priori' Hypotheses:** *A priori*, we expect that patients who are screened more frequently will have a shorter time to successful extubation regardless of the SBT technique used. We do not expect SBT technique alone to influence the time to successful extubation or successful extubation rate.

**2.3 Study Population:** We will include 760 COVID-19 negative and up to 250 COVID-19 positive critically ill adults [ $\geq 18$  years of age (USA) or  $\geq 16$  years of age (Canada) or admitted to an adult ICU] who are receiving invasive ventilation for at least 24 hours in 20 North American ICUs. Based on our pilot trials, we expect to recruit, on average, 1 out of every 5 patients screened by research personnel (1 in 5 for RELEASE; 1 in 5.3 for SENIOR) or 2.58 patients/ICU per month over a 31 month recruitment period. To be conservative, we expect to recruit 2 patients/ICU per month.

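### The O'Brien-Fleming boundary chosen out of caution about benefit also governs reintubation rate, with no separate harm threshold, so it is very insensitive to reintubation harm at the 25% look

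*Combined protocol and SAP*

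**What the plan says.** Section 2.11.4 describes the looks as "Interim analyses for safety (adverse events) and efficacy (primary outcome"), which "will be performed at 25%, 50% and 75% of accrual". It then says: "Given the risks of stopping early for benefit, statistical significance will be declared using small p-values", using O'Brien-Fleming "boundaries for the primary outcome (time to successful extubation) and reintubation rate". It does not give a direction for reintubation, a threshold specific to harm, or the action that follows a crossing. Adverse events are reviewed at the same looks with no boundary attached, and section 1.6 names a Data Safety and Monitoring Committee (DSMC).

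Section 1.1 sets out why reintubation matters: "premature or failed attempts at extubation necessitating reintubation are associated with morbidity (VAP) and an 8 to 10 fold increase in mortality".

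Section 2.1a has two primary comparisons on one outcome, screening frequency and SBT technique. Section 2.12.2 says that, without interaction, the main effects "will have the same power to detect the same size differences". Section 2.11.4 does not say which of the two comparisons its efficacy boundary is for.

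**The concern.** O'Brien-Fleming boundaries demand extreme evidence early, so that a trial is not stopped on an unstable early benefit. That is the reason section 2.11.4 gives, and for the primary outcome it is sound. It does not carry over to harm, where the committee needs a prompt for closer review well short of overwhelming proof.

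Reintubation is the harm at the centre of the trade-off in section 1.1, and earlier extubation is the route by which more frequent screening is meant to work. If the only stated criterion for reintubation is the efficacy boundary, a large early excess could sit below it and be recorded as not significant.

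**Working it through.** **Inputs from the protocol.** Looks at 25%, 50% and 75% of accrual plus a final analysis (2.11.4). N = 760, HR 1.25, medians 5.0 and 4.0 days, 80% power, alpha 0.05, combined mortality hazard 3.2% per patient-day (2.12.2).

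**Assumptions.** Two-sided alpha; 380 per arm for each factor; accrual counted on the 760 COVID-19 negative patients; reintubation base rates of 10% and 15%, because the documents give none.

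**1. The plan's own figure.** Events = 4(1.96 + 0.8416)² / (ln 1.25)² = 631. With constant hazards, the probability of successful extubation is (ln2/5)/(ln2/5 + 0.032) = 0.812 and (ln2/4)/(ln2/4 + 0.032) = 0.844, mean 0.828. N = 631/0.828 = 762, or 781 with a four-look O'Brien-Fleming inflation of 1.025. Both are within 3% of 760, so the planning model is reproduced and its extubated fraction can be used below.

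**2. Boundaries.** z = 2.024/√t gives 4.05, 2.86, 2.34 and 2.02; nominal two-sided p = 0.00005, 0.0042, 0.019 and 0.043.

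**3. Extubated patients per arm.** 380 × t × 0.83 = 79, 158 and 237 at the three looks. Some patients will still be ventilated at each look, so these are if anything high.

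**4. What the 25% look needs.** Solve (x − 0.15)/√(2p̄(1 − p̄)/79) = 4.05, where p̄ is the mean of x and 0.15. This gives x of about 0.44: 15% in one arm must be met by about 44% in the other, or roughly 12 against 35 reintubated of 79.

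**5. Chance of flagging a true doubling at the 25% look.** Power = Φ[(Δ − z√(2p̄(1 − p̄)/n)) / √((p₀(1 − p₀) + p₁(1 − p₁))/n)]. For 15% vs 30% with n = 79, the two root terms are 0.0664 and 0.0654.
- O'Brien-Fleming: (0.15 − 4.05 × 0.0664)/0.0654 = −1.82, so 3%.
- Nominal p<0.01: (0.15 − 2.576 × 0.0664)/0.0654 = −0.32, so 37% (38% when binomial counts are simulated).

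Chance of a flag at each look, from simulated binomial counts:

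| Look | 15% vs 30%: O'Brien-Fleming | 15% vs 30%: p<0.01 | 10% vs 20%: O'Brien-Fleming | 10% vs 20%: p<0.01 |
|---|---|---|---|---|
| 25% | 3% | 38% | 1% | 20% |
| 50% | 64% | 74% | 35% | 47% |
| 75% | 95% | not proposed | 77% | not proposed |

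Counting all randomised patients (95 per arm per look) gives cumulative O'Brien-Fleming figures of 5/75/98% for 15% vs 30% and 1/45/86% for 10% vs 20%. For a smaller harm, 10% vs 15%, they are 0.1/8/30%.

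**6. False triggers of a p<0.01 guideline over the first two looks.** Each look contributes 0.5% in one direction. Allowing for the correlation between looks gives 0.9% per factor in one direction and 1.8% per factor in either direction. Across two independent factors in either direction: 1 − (1 − 0.0176)² = 3.5%.

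**7. The factorial question.** With 760 × 0.828 = 629 events, the drift is ln(1.25) × √629/2 = 2.80. Screening at HR 1.25 then crosses by the 25%, 50% and 75% looks with cumulative probability 0.4%, 19% and 54%. If a crossing ended all recruitment, SBT power at HR 1.25 would fall from 79% to about 59%. If SBT randomisation continued, it would stay at about 79%.

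**The case against.** The boundary is not the only safeguard. Adverse events are reviewed at every look with no boundary attached, a DSMC exists, and nothing says that it may act only on a crossing. Success on the primary outcome needs at least 48 hours of sustained unsupported breathing (2.10.1), so early reintubation also counts against an arm there. The base rates are assumed. With 79 patients per arm any cautious rule is weak: p<0.01 itself misses a doubling 62% to 80% of the time at the first look. All of this stands. It limits the point to the earliest monitoring, but it does not supply a reason for judging harm by a boundary justified only by caution about benefit.

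Two stronger readings are tempting, and neither is supported.

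- A reader might infer that interim monitoring is blind to reintubation harm throughout. For a doubling that describes only the 25% look. At 50% the disadvantage against p<0.01 is 10 to 12 percentage points, and at 75% detection is 77-95%.
- A reader might infer that a crossing on screening frequency stops the trial and cuts short the SBT comparison. Section 2.11.4 names no factor and no action, and closing one factor while continuing the other is fully compatible with it. What is missing is detail. The fall to 59% is conditional on a trial-wide stop that the text does not prescribe, and section 2.2 expects no SBT effect on this outcome. The reverse case, an SBT crossing affecting screening, is equally open.

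**Conclusion.** The point holds for reintubation at the earliest look. A boundary justified by caution about benefit is also the only stated criterion for a harm that the protocol treats as grave. At 25% of accrual it would flag a true doubling in about 1 to 3 of 100 trials, where a p<0.01 guideline would flag about 20 to 38. The gain is modest at 50%, and no change is needed at 75% for a harm of that size. These figures rest on assumed base rates of 10-15%, 1:1 allocation on each factor, two-sided alpha and about 83% of patients extubated.

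The silence on which primary comparison the efficacy boundary serves is a secondary matter of clarification. Part of the protocol between the recruitment table in section 2.13 and section 3.1.5 was not available for this review. It may contain monitoring text that settles either matter.

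**What to change.** First check the protocol text before section 3.1.5 and any DSMC charter for existing monitoring rules. If they do not cover this, amend section 2.11.4 and the charter:

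1. Keep O'Brien-Fleming for claims of benefit on time to successful extubation.
2. Add, for each factor, a separate non-binding guideline for reintubation harm, with its direction stated. One example is nominal two-sided p<0.01 at the 25% and 50% looks and the O'Brien-Fleming value (p = 0.019) at 75%. Show deaths before extubation beside it, since patients who die cannot be reintubated. The exact threshold is for the sponsor and DSMC to choose.
3. State that the efficacy boundary is applied to each factor separately and that a crossing closes that factor only.

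The cost is wording, plus false alarms under no effect over the first two looks: 0.9% per factor in one direction, 1.8% per factor in either direction, and 3.5% across both factors in either direction. Because the guideline is non-binding, a false alarm leads to committee review and not to an automatic stop.
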